## 6.2 Planned analysis of primary outcome

The analysis of the primary outcome will be based on the intention-to-treat dataset and based on unimputed data. All tests will be two-sided with  $p < 0.05$ .

Descriptive data on days of methamphetamine use will include the median number of days at each time point (baseline, week 4, week 8, week 12 and week 20), with interquartile ranges reported. Variance estimates (i.e., standard errors and confidence limits) will be bootstrapped.

The main effect of medication on days of methamphetamine use will be tested using a mixed model with a group (placebo [0] vs. mirtazapine [1]) by time (baseline [0], week 4 [1], week 8 [2], week 12 [3]) interaction effect, with time entered as a factor variable, producing individual effect estimates for each time point and making no assumptions about the linearity of changes over time. The primary timepoint is week 12. A negative binomial generalised linear mixed model will be used to test this effect. As noted under the general principles above, a random intercept term will be included in the model to account for clustering on repeats [31], and a random intercept term will be included in the model to account for site only if this significantly improves model fit (based on a likelihood ratio test;  $p < 0.05$ ).

Days of methamphetamine use in this model will be based on the past 28 days prior to baseline, and since the previous assessment at the week 4, 8 and 12 assessments (up to 35 days prior to the assessment). Days when the participant was incarcerated or hospitalised will be censored, as per the TLFB guidelines. An exposure term (i.e. offset) will be included in the model to adjust for the exact number of days in each of these periods, because this can vary depending on the actual assessment dates and censoring.

*Interpretation of the treatment effect from the model (i.e., interaction effect rate ratio):* The main treatment effect will be the time (baseline vs. active medication phase) x condition (active vs. placebo) interaction effect, with the primary timepoint being week 12. This interaction effect represents the rate ratio of change in days of methamphetamine from baseline to follow-up (i.e., rate of days of use at baseline/rate of days of use at follow-up) for the active condition, over the rate ratio of change from baseline to follow-up for the placebo condition. That is:

$$r = (\text{days of use at follow-up} / \text{days of exposure at follow-up}) / (\text{days of use at baseline} / \text{days of exposure at baseline})$$

$r_p = r$  in placebo group

$r_a = r$  in active group

The interaction coefficient representing the treatment effect is the rate ratio (rr) of these two parameters, i.e.,  $r_a/r_p$ .

Thus, the interaction term can be interpreted as the relative difference in the rate of *change* between the intervention and control groups, which allows for random misbalance at baseline rather than assuming baseline methamphetamine use is the same in both groups.

*Analysis of the primary outcome at week 20:* A separate analysis will be conducted to compare days of methamphetamine use in the past 4 weeks at the week 20 assessment. We have chosen to analyse the week 20 endpoint separately because we believe that (a) differences in the conduct of the week 20 assessment may impact data variability (e.g., phone interviews and greater attrition), and (b) there are differences in the clinical interpretation of the outcome at the week 20 assessment (because

participants are no longer on the trial intervention and are offered off-label mirtazapine and other substance use treatment prior to week 20). We will test the main effect of the trial medication on days of methamphetamine use at week 20 using a mixed model with a group (placebo [0] vs. mirtazapine [1]) by time (baseline [0], week 20 [1]) interaction effect. A negative binomial generalised linear mixed model will be used to test this effect. An exposure term (i.e. offset) will be included in the model to adjust for the exact number of days in each of these periods if the observed number of days in the TLFB varies from 28 days. As noted under the general principles, a random intercept term will be included in the model to account for clustering on repeats [31], and a random intercept term will be included in the model to account for site only if this significantly improves model fit (based on a likelihood ratio test;  $p < 0.05$ ).

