## 3.2 Randomisation

Eligible participants are randomly assigned (1:1) to receive either placebo or mirtazapine based on a computer-generated permuted block randomisation sequence with variable block sizes, stratified by site, sex (male vs. female or other) and depression (PHQ-9 score < 10 vs. 10 or greater) assessed at eligibility.

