## 6 Analysis

### 6.1 General approach to planned analyses

The analysis plan below is based on blinded data that did not include the treatment allocation variable. After unblinding, model assumptions will be checked (e.g., distribution of the outcome, cell sizes and model convergence and model fit) and models will be modified as necessary; any covariates that need to be included in the model will be identified.

Descriptive statistics will be presented as the mean (standard deviation) for continuous parametric measures and median (inter-quartile range) for highly skewed measures. Categorical variables will be presented as a percentage per category. Baseline descriptive statistics will be compared between the treatment conditions using appropriate inferential statistics. Bootstrapped confidence intervals will be used for outcomes that are highly skewed.

As a general principle, linear models will be used for normally distributed continuous outcomes. A logistic link will be used for categorical outcomes. A Poisson or negative binomial link will be used for count data and may be used for categorical outcomes with small cell sizes where this produces superior model fit. If model assumptions are breached, other model options will be examined to identify the best model fit.

A random intercept term for participant identifier will be included in all models with time-varying data model to account for clustering of data on repeated assessments. A random intercept for site will be included in models only if this significantly improves model fit (based on a likelihood ratio test;  $p < 0.05$ ).

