#### **Abstinence (negative oral fluid samples)**

Descriptive data on the proportion of negative oral fluid samples in each group across the active trial phase will be presented. The effect of mirtazapine on methamphetamine negative oral fluid samples (no [0], yes [1]) will be tested using a group contrast (placebo [0] vs. mirtazapine [1]) across all follow-up time points (weeks 4, 8 and 12) to obtain an average treatment effect across the 12-week intervention period. A generalised linear mixed model with a logistic link will be used to test this effect.

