## 6.6 Additional analyses

The following analyses may be done after the primary analysis to supplement the primary analyses or as separate research papers.

Subgroup analyses: Subgroup analyses are planned for the sub-groups of (1) depressed (PHQ-9 score 10 or greater at eligibility), (2) not depressed (PHQ-9 score of < 10 at eligibility), (3) participants who reported being male at birth, and (3) participants who reported being female or other sex at birth. The randomisation was stratified on these subgroups, meaning that participants are randomly assigned to condition within each subgroup.

Per-protocol analysis: A set of per-protocol analyses will be undertaken on the per-protocol dataset. This may be done for the primary and secondary end-points and for any sub-group analyses. The per protocol analysis will use non-imputed data. These models will incorporate adjustment to account for any group differences in baseline characteristics.

Treatment complier effect: A set of treatment complier analyses may be conducted on the treatment complier dataset. This may be done for the primary and secondary endpoints and for any sub-group analyses. Treatment complier analysis will incorporate adjustment to account for any group differences in baseline characteristics.

Average treatment effect: Additional analyses may be conducted that repeat the primary and secondary analyses but which collapse the follow-up data across the week 4, 8 and 12 follow-up time points (i.e., baseline [0] vs. week 4 [1], week 8 [1], week 12 [1]) such that the outcome is the average treatment effect across the 12-week trial medication period.

Covariate adjustment. Analyses of the primary outcome measure will be repeated with adjustment for a set of prognostic variables, as per the recommendations of Kahan et al. [32], to improve model precision and aid interpretation of the main analyses of the primary outcome. These prognostic variables will include: age, sex (male vs. female or other), methamphetamine use days in the past 4 weeks at eligibility, main route of methamphetamine administration (injecting vs. other routes), and PHQ-9 depression score at eligibility. All of these variables were collected at the eligibility assessment, prior to randomisation, and therefore they are not collider variables.

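### Sex and PHQ-9 stratum, both used to stratify randomisation, are named in no primary or secondary model, and site enters only after a significance test: a modest, conservative loss that bears mainly on abstinence and PGI

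*Combined protocol and SAP*

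**What the plan says.** SAP section 3.2 states that randomisation was "stratified by site, sex (male vs. female or other) and depression (PHQ-9 score < 10 vs. 10 or greater) assessed at eligibility".

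Section 6.2 tests the primary outcome "using a mixed model with a group (placebo [0] vs. mirtazapine [1]) by time" interaction in a negative binomial mixed model with an offset and a participant intercept. Sex and PHQ-9 stratum are not among the terms. The week 20 model has the same form.

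For site, section 6.1 sets one rule for all models: "A random intercept for site will be included in models only if this significantly improves model fit". Section 6.2 repeats it for the primary outcome: "a random intercept term will be included in the model to account for site only if this significantly improves model fit". Section 6.1 also adds that after unblinding "any covariates that need to be included in the model will be identified", without naming any.

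In section 6.3 the depression, sleep, quality-of-life and HIV-risk models are group by time with no stratum named. Abstinence is a group contrast over weeks 4, 8 and 12: "A generalised linear mixed model with a logistic link will be used to test this effect". No covariate is named and there is no baseline sample. The PGI model in section 6.4 has the same follow-up-only form.

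Under covariate adjustment, section 6.6 says: "Analyses of the primary outcome measure will be repeated with adjustment for a set of prognostic variables". The list is age, sex, days of use at eligibility, route of administration and PHQ-9 score at eligibility. Site is not on it, no secondary outcome is covered, and the section as a whole describes analyses that may be done after the primary one.

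**The concern.** Stratified randomisation makes the arms more alike on the strata than chance would. A model that leaves the strata out keeps their variation in its error or participant-intercept variance. It therefore reports a standard error for a less balanced design than the one used. Intervals come out too wide and the test rejects less often than 5% under the null.

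Three features of the plan make this worth settling. Site is a design factor, but its place in the model depends on a test of a variance component, which has limited power when sites are few. Covariates may be chosen after unblinding, so the main models are not fully fixed in advance. Abstinence is the only biologically verified efficacy outcome and negatives are scarce, yet its model makes no use of baseline methamphetamine days, which Table 4 shows as complete for all 339 participants.

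**Working it through.** **Inputs.** From the SAP: 1:1 allocation; two-sided 5% tests (section 5.1); 339 in the ITT dataset; 31, 33 and 36 negative samples at weeks 4, 8 and 12 among 797 results (Table 6). Not in the documents, so assumed: the share of variance explained by the strata (R²), the number of sites, and the site intraclass correlation (ICC).

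**The plan's own figure.** In section 3.3 the attrition step reproduces: 255 / 0.75 = 340. The 255 cannot be derived because no dispersion is given. Nothing below depends on it.

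**Follow-up-only contrasts (abstinence, PGI), linear approximation.** With strata balanced by design and omitted from the model:

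- SE ratio = 1/√(1−R²)
- True size = 2[1−Φ(1.96/√(1−R²))]
- Take an effect for which the unadjusted formula gives 90% power, so effect/SE = 1.960 + 1.282 = 3.2415. Actual power is then Φ((3.2415−1.96)/√(1−R²)) unadjusted and Φ(3.2415/√(1−R²)−1.96) adjusted.

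| R² | SE ratio | True size | Power unadjusted | Power adjusted |
|---|---|---|---|---|
| 0.05 | 1.026 | 4.4% | 90.6% | 91.4% |
| 0.10 | 1.054 | 3.9% | 91.2% | 92.7% |
| 0.20 | 1.118 | 2.8% | 92.4% | 95.2% |

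At R² = 0.02 the true size is 4.8%, which is negligible.

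**Abstinence by simulation.** 4,000 trials per scenario, stratified permuted blocks, N = 339, 6 sites assumed, linear regression on each participant's proportion negative in place of the planned logistic mixed model. With in-sample R² near 8%, size was 4.4% unadjusted and 5.0% adjusted, and power 83% and 85%. Near 16%, size was 3.9% and 5.6%, and power 81% and 86%. Monte Carlo error for size is about 0.3 points. In-sample R² flatters the strata: with 7 stratum terms and 338 degrees of freedom, 7/338 = 2.1% appears with no true effect.

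**Group-by-time contrasts.** Same design, analysing week 12 minus baseline on a log scale. Strata affecting only the level of use cancelled: size 5.2% unadjusted, 5.1% adjusted. Where sex and PHQ-9 stratum each shifted the change by 0.3 or 0.6 log units, unadjusted size fell to 3.9% or 2.7%. Adjusting the change for the strata gave 4.7% or 5.1%.

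**Site pre-test.** A one-way random-effects F test stands in for the likelihood ratio test. With S sites and m = 339/S per site, power = P(F > F₀.₉₅/(1 + m·ICC/(1−ICC))). For 4 to 8 sites:

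| ICC | Chance that site is kept |
|---|---|
| 0.01 | 19–24% |
| 0.02 | 37–41% |
| 0.05 | 70–73% |

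**Events.** 31 + 33 + 36 = 100 negatives; 100/797 = 12.5%.

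**Parameters.** A full site, sex and PHQ-9 by time specification adds (S−1+1+1) × 4 = 4(S+1) fixed terms over four time points: 20, 28 or 36 for 4, 6 or 8 sites, on top of the present 2 × 4 = 8. Sex and PHQ-9 by time alone add 2 × 4 = 8.

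**The case against.** The best answer is that little is at risk. The error is conservative, so no positive result is undermined. The primary outcome and most secondary outcomes are analysed as change from baseline, where level effects of the strata cancel, and the documents give no evidence that the strata predict change. Baseline PHQ-9 is already in the depression model as part of the outcome vector. Section 6.6 repeats the primary analysis with sex and PHQ-9 score, two of the three stratification factors. Week 12 assessments number 293, against the 255 required. All of this stands, and it limits the size of the point. It does not remove it: section 6.6 leaves out abstinence, PGI and site, and a clause allowing covariates to be identified after unblinding is no substitute for naming them beforehand.

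A reader might go further in four ways that the documents do not support.

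- That the abstinence model adjusts for nothing. Section 6.1 says "A random intercept term for participant identifier will be included in all models with time-varying data model", and site may enter if its test is significant. What is missing is any named covariate.
- That site will usually be dropped. That is so only if its effect is small; at an ICC of 0.05 it is kept in about 70% of trials, under the assumed number of sites.
- That the primary interval is too wide. This requires strata that predict change.
- That adjustment costs only a few degrees of freedom. Full strata-by-time terms cost 20 to 36 parameters for 4 to 8 sites.

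**Conclusion.** The omission is plain from the text: three stratification factors, two of them in no primary or secondary model and the third subject to a pre-test. The consequence is a modest loss of precision and power with no false-positive risk.

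It bears most on abstinence and PGI. There, if the strata explain 5% to 20% of variance, the standard error is about 3% to 12% too large, the true size is about 4.4% to 2.8%, and 0.8 to 2.8 points of power are lost around the 90% level. The R² range is an assumption, and the formula is linear while the abstinence model is logistic. The abstinence simulation, also linear, showed a power gain of about 2 to 5 points in its two scenarios.

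For the primary outcome, depression, sleep, HIV risk and quality of life, nothing is lost unless the strata predict change. The omission itself is certain; its size is not.

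**What to change.** Amend the SAP before unblinding:

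1. Delete the likelihood ratio rule for site. Keep site in every primary and secondary model whatever its significance, as a random intercept where fixed site effects would be sparse, as in the abstinence model with about 100 negatives in 797 samples.
2. Add sex, PHQ-9 stratum and baseline methamphetamine use rate as main effects to the abstinence and PGI models. Use the rate rather than the count, because section 4.7 shows that observed baseline days run from 16 to 28.
3. In the group-by-time models, pre-specify sex and PHQ-9 stratum with their interaction with time. Main effects suffice if baseline is moved from the outcome vector to a covariate.
4. Report the unadjusted models as sensitivity analyses.

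No new data are needed. With site as a random intercept, item 3 adds 8 fixed terms to a four-time-point model; adding fixed site-by-time terms as well would bring the total to 4(S+1). The logistic model may fail to converge, so the SAP should state a fallback, for example the order in which terms are dropped. The open clause on covariates in section 6.1 should then be closed or confined to sensitivity analyses.

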## 3.3 Sample size

The estimated sample size required for the study (N = 340; 170 per group) was to enable us to detect a minimum rate ratio of 0.75 on our primary outcome (equivalent to a relative reduction from 25 days methamphetamine use in the past 4 weeks at baseline to 20 days use in the past 4 weeks at week 12) with 90% power (two-tailed test,  $p = 0.05$ ). This sample size calculation was based on the effect size found in the most recent trial of mirtazapine for methamphetamine dependence [15] and allows for up to 25% attrition (ie., a final sample of at least 255, or 128 per group, at week 12).

We randomised 344 participants in the trial, of whom 339 participants received the trial medication and 293 completed their week 12 assessment, meeting the sample size requirements estimated above.

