## 5 Statistical Principles and definitions

### 5.1 Confidence intervals and p values

All tests will be two-tailed. Significance will be  $p < 0.05$  for all outcomes. Confidence intervals will be 95%.

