#### **Depression**

The effect of mirtazapine on depression will be tested using a mixed model using a group (placebo [0] vs. mirtazapine [1]) by time (baseline [0] vs. weeks 4 [1], week 8 [2], week 12 [3]) interaction, with time entered as a factor variable, producing individual effect estimates for each time point and making no assumptions about the linearity of changes over time. The primary timepoint for this endpoint is week 12. A generalised linear mixed model will be used to test this effect.

The effect of mirtazapine on depression at week 20 will be tested using a separate analysis. We will test the main effect of the trial medication on depression at week 20 using a mixed model with a group (placebo [0] vs. mirtazapine [1]) by time (baseline [0], week 20 [1]) interaction effect. A generalised linear mixed model will be used to test this effect. We have chosen to analyse the week 20 endpoint separately because we believe that (a) differences in the conduct of the week 20 assessment may impact data variability (e.g., phone interviews and greater attrition), and (b) there are differences in the clinical interpretation of the outcome at the week 20 assessment (because participants are no longer on the trial intervention and are offered off-label mirtazapine and other substance use treatment prior to week 20).

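### Taking the effect as a difference in change from a free baseline probably costs precision on the secondary scales, possibly on days of use, and leaves the Section 6.6 adjustment little to do

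*Combined protocol and SAP*

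**What the plan says.** SAP Section 6.2 fits a negative binomial mixed model to days of use at baseline and weeks 4, 8 and 12, with a participant random intercept. The effect is the group-by-time interaction at week 12: the follow-up to baseline rate ratio on mirtazapine divided by the same ratio on placebo. The SAP gives its reason openly: this form "which allows for random misbalance at baseline rather than assuming baseline methamphetamine use is the same in both groups".

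Section 6.3 uses the same structure for depression, a group "by time (baseline [0] vs. weeks 4 [1], week 8 [2], week 12 [3]) interaction", and again for sleep, quality of life and HIV risk. Section 6.4 uses it for anxiety. The separate week 20 analyses of days and depression also contrast change from baseline. Abstinence and patient impression have no baseline row and are not affected.

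Section 6.6 repeats the primary analysis with age, sex, eligibility days of use, main route and eligibility PHQ-9, "to improve model precision and aid interpretation of the main analyses of the primary outcome". All five are fixed eligibility values, and no covariate-by-time term is mentioned.

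**The concern.** In a randomised trial, a baseline difference between the arms is chance. The planned contrast subtracts the whole of it. A baseline covariate subtracts only the part that carries forward to follow-up, so it too allows for imbalance; the SAP's stated reason does not separate the two approaches. In large samples and a linear model, the covariate analysis is never the less precise of the two.

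Four of the five secondary hypotheses rest on such contrasts, and on all four scales the Table 6 IQR is wider at baseline than at week 12. That is where subtracting the full baseline difference costs most.

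Section 6.6 has a related problem. A covariate that is constant within a person, entered as a main effect, has little purchase on a within-person contrast. The adjusted analysis may then look much like the unadjusted one for structural reasons, and a reader could take that agreement for robustness.

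**Working it through.** **1. The plan's own figure.** Section 3.3 states "N = 340; 170 per group", "to detect a minimum rate ratio of 0.75 on our primary outcome", "with 90% power (two-tailed test" at 0.05. The attrition step reproduces: 255/(1 − 0.25) = 340. The core 128 per group cannot be rebuilt, because no dispersion, SD or baseline to follow-up correlation is given. Working backwards, SE(log rate ratio) = |ln 0.75|/(1.960 + 1.282) = 0.0887, or an SD of 0.0887 × √(128/2) = 0.71 per participant. The SAP does not show which contrast that SD belongs to, so no power shortfall can be stated.

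**2. Formula.** In a linear random-intercept model with complete data, the interaction is the difference in mean change. Put the week 12 SD at 1, the baseline SD at k and the correlation at ρ. The change variance is k² + 1 − 2ρk, and the variance after a baseline covariate is 1 − ρ². The ratio is (1 − ρ²)/(k² + 1 − 2ρk), and the share of a baseline difference that carries forward is ρ/k.

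**3. Numbers in.** k is the ratio of Table 6 IQR widths, a rough proxy for the SD ratio. ρ of 0.4 to 0.6 is an assumption.

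| Outcome | Width, baseline / week 12 | k | Ratio at ρ = 0.4 / 0.5 / 0.6 | Carried forward at ρ = 0.5 |
|---|---|---|---|---|
| PHQ-9 | 9 / 7 | 1.29 | 0.52 / 0.55 / 0.58 | 0.39 |
| AIS-5 | 6 / 4 | 1.50 | 0.41 / 0.43 / 0.44 | 0.33 |
| HRBS | 6 / 5 | 1.20 | 0.57 / 0.60 / 0.64 | 0.42 |
| EQ-5D | 0.12 / 0.11 | 1.09 | 0.64 / 0.68 / 0.73 | 0.46 |
| GAD-7 | 9 / 9 | 1.00 | 0.70 / 0.75 / 0.80 | 0.50 |
| Days, raw scale | 11 / 15 | 0.73 | 0.88 / 0.93 / 0.97 | 0.68 |
| Days, log scale | ln(28/17) = 0.499 / ln(24/9) = 0.981 | 0.51 | 0.99 / 1.00 / 0.99 | 0.98 |

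For PHQ-9 at ρ = 0.5, a 1-point chance difference calls for a correction of about 0.39 point; the planned contrast takes off 1. A ratio of 0.55 is worth 1/0.55 = 1.8 times the participants.

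**4. Stratification.** Section 3.2 stratifies on eligibility PHQ-9 (below 10 or not). Simulating that, with an assumed eligibility to baseline correlation of 0.7 to 0.8, moved the PHQ-9 ratio from about 0.50–0.56 to about 0.60–0.69. The SD of the baseline difference fell by about 15% to 23%.

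**5. Days of use in the planned model type.** Negative binomial random-intercept models were fitted to simulated trials: 339 participants, no treatment effect, 7/11/14% missing completely at random, 150 datasets per setting. The comparator held the arms equal at baseline. In a linear model that is close to a baseline covariate; here it is only a stand-in. The slope is that of the estimate on the chance baseline log-ratio; zero means imbalance is handled correctly.

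| Data | ρ | Variance, constrained/planned | Slope, planned | Slope, constrained |
|---|---|---|---|---|
| From the planned model | 0.5 | 0.78 | −0.48 | −0.03 |
| Matched to Table 6 quartiles | 0.3 | 0.84 | −0.71 | +0.20 |
| Matched to Table 6 quartiles | 0.5 | 0.88 | −0.56 | +0.10 |
| Matched to Table 6 quartiles | 0.7 | 0.99 | −0.22 | +0.10 |

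The gain runs from 1% to 22%, with Monte Carlo error of several percent. Had the planned contrast 90% power, these ratios would lift it to between 90.2% and 95.7%.

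**6. Section 6.6.** Adding eligibility days (the only one of the five covariates simulated) to the planned model multiplied its variance by 0.98 to 1.04, and adjusted and unadjusted estimates correlated 0.986 to 0.995. Covariate-by-time terms gave 0.98 to 1.03. In the constrained model, the same covariate took the variance, relative to the planned model, from 0.78 to 0.63 (planned-model data), and from 0.84 to 0.81, 0.88 to 0.89 and 0.99 to 0.91 (Table 6-like data, ρ = 0.3, 0.5, 0.7).

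**The case against.** The contrast is fully defined and openly justified, and Section 5.4 defines the primary outcome as a change from baseline. A reader might infer that the primary test is biased or invalid. It is not: over repeated randomisation the estimate is unbiased, and what remains is efficiency and a bias conditional on the imbalance observed. All of this stands.

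A reader might also infer that the primary analysis clearly wastes precision and over-corrects imbalance. The documents do not establish that. The model has a log link, and on the log scale the Table 6 quartiles give a ratio of 0.99 to 1.00. There the carried-forward share reaches 1 near ρ = 0.51; above that, the change contrast would under-correct. The simulated mixed model over-corrected throughout, so the evidence is mixed and turns on a correlation the SAP does not give.

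IQR width is a weak proxy where a scale sits at its floor (AIS-5, week 12 median 1) or ceiling (EQ-5D, upper quartile 1.00). Sections 6.1 and 6.3 leave the distribution for these scales open, so the linear formula may not apply exactly. That limits the figures more than their direction.

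The claim that the planned model cancels the Section 6.6 covariates is exact only for a linear model with complete data. This one is negative binomial, with 339 − 293 = 46 participants lacking week 12. Section 6.6 also has an interpretive purpose and does not call the adjusted analysis a robustness check; that misreading is a risk, not something the SAP commits.

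**Conclusion.** The point holds as one of efficiency, not validity. The loss is likely material for PHQ-9, AIS-5, HRBS and EQ-5D: a variance ratio of roughly 0.4 to 0.7, and about 0.6 to 0.7 for PHQ-9 with stratification. This rests on an assumed correlation of 0.4 to 0.6, IQR width as a proxy for SD, and a linear model. For days of use the gain lies between about nil and about 20% of the variance, and over-correction is not assured. Under the planned model, the Section 6.6 adjustment can do little for precision, so its agreement with the unadjusted result carries little weight. The week 0 assessment follows randomisation but precedes medication, and only 5 of 344 missed it, so treating baseline differences as chance remains reasonable.

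**What to change.** Before unblinding:

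- Model weeks 4, 8 and 12 as outcomes with group by time and the baseline value as a covariate, with week 12 as the primary contrast. For days, use the log baseline rate; Section 4.7 gives a baseline range of 1 to 28, so the log is defined.
- Use participant-level robust or bootstrapped standard errors. A constrained-baseline negative binomial mixed model with model-based errors showed 10% to 14% type I error in simulation. No error rate was obtained for the planned or the covariate model, so simulate the chosen model before fixing it.
- Do the same for PHQ-9, AIS-5, HRBS, EQ-5D, GAD-7 and the week 20 analyses.
- Add the Section 6.6 covariates to this model as main effects. Covariate-by-time terms in the planned model are not a useful substitute.
- Keep the planned difference in change, on the full ITT set, as a sensitivity analysis.

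The cost is SAP wording; the data are already collected. The downside to state is that the 20 treated participants with no later assessment leave the model, so it uses the modified ITT set (at most 339 − 20 = 319). They add almost nothing to the planned contrast. Table 4 also shows missing baseline values for PHQ-9 (3), GAD-7 (2) and EQ-5D (1), which need a stated rule. Section 6.1 leaves covariates to be identified after unblinding, so naming baseline now removes one post-hoc choice. If unblinding has already happened, report the baseline-adjusted model as a labelled supplementary analysis.
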